#### 8.5.2.3. Dihydroartemisinin-piperaquine for post-discharge malaria chemoprevention

The study will use the following formulation of Dihydroartemisinin-piperaquine: Eurartesim® from Sigma Tau, Italy, another brand of DP similar to the Duo-Cotecxin brand approved by the Kenyan and Ugandan regulatory authorities. Eurartesim is a co-formulated tablet containing 40 mg dihydroartemisinin and 320 mg piperaquine phosphate or as 20/160 (paediatric formulation).

#### 8.5.2.4. Dihydroartemisinin-piperaquine dosing regimen

Dosing will be by bodyweight according to the following schedule recommended by WHO's Guidelines for the treatment of malaria, 3rd edition from April 2015 (Table 4).

*Table 4: Dihydroartemisinin-piperaquine weight-based dosing schedule*

| weight in Kg        | Daily dose (mg) |     | Tablet strength and number of tablets per dose                     |
|---------------------|-----------------|-----|--------------------------------------------------------------------|
|                     | Piperaquine     | DHA |                                                                    |
| 5 to <8   | 160             | 20  | 1 x 160 mg / 20 mg tablet or
½ x 320 mg / 40 mg tablet   |
| 8 to <11  | 240             | 30  | 1.5 x 160 mg / 20 mg tablet or
¾ x 320 mg / 40 mg tablet |
| 11 to <17 | 320             | 40  | 1 x 320 mg / 40 mg tablet                                          |
| 17 to <25 | 480             | 60  | 1.5 x 320 mg / 40 mg tablet                                        |
| 25 to <36 | 640             | 80  | 2 x 320 mg / 40 mg tablet                                          |

If the paediatric strength tablets are not available, the full tablet strength can be used to provide the equivalent dose in mg (i.e. ¼ tablet and ½ tablet of 320 / 40 mg tablets for the first two weight bands).

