#### 8.5.2.6. Placebo DP

Placebos for DP will be manufactured by Sigma Tau, Italy. The dosage regimen for DP-placebo will be identical in number of tablets per day and timing of the dose to that of the active DP product. The drug administration procedures will also be identical to that for the active drugs.

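### Table 4 and the note beneath it give different full-strength tablet fractions for the two lowest weight bands; the note yields 50% and 67% of the tabulated dose

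*Protocol*

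**What the plan says.** Section 8.5.2.3 names two tablet strengths (piperaquine/DHA): 320/40 mg and a paediatric 160/20 mg.

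Table 4 in section 8.5.2.4 sets the daily dose by weight band, in milligrams and in tablets. For the two lowest bands it offers either strength:

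- 5 to <8 kg, 160/20 mg daily: "1 x 160 mg / 20 mg tablet" or "½ x 320 mg / 40 mg tablet".
- 8 to <11 kg, 240/30 mg daily: "1.5 x 160 mg / 20 mg tablet" or "¾ x 320 mg / 40 mg tablet".

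The note directly below the table covers the case where paediatric tablets cannot be had. It says that "the full tablet strength can be used to provide the equivalent dose in mg", and then specifies "¼ tablet and ½ tablet of 320 / 40 mg tablets for the first two weight bands".

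The dose is also an analysis variable. Section 9.2.5.2, item 14, plans a subgroup analysis by terciles of the mg/kg dose received. It hypothesises that variation in mg/kg is small, arises from body weight within the fixed bands, and will not affect efficacy.

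**The concern.** The table and the note address the same children, the same tablet and the same circumstance, yet give different fractions. Someone preparing a dose from full-strength tablets has two instructions and cannot satisfy both. The note also contradicts itself, because its fractions do not deliver the milligram equivalence it claims.

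If paediatric tablets ran out and the note was followed in some places, children in the same band could receive different doses depending on site or supply. The conflict is confined to the lightest children. The protocol describes piperaquine's QTc effect as dose-dependent (section 11.8.1.2) and, from a trial in adults, links protection to trough piperaquine concentration (same section). An ambiguous dose therefore bears on both safety and protection. The premise of subgroup item 14 would also fail, since part of the mg/kg variation would come from which instruction was used and not from body weight.

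**Working it through.** **Inputs.** Tablet contents are from section 8.5.2.3. The tabulated doses and fractions, and the note's fractions, are from section 8.5.2.4.

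**Formula.** Dose = tablet fraction × tablet content, compared with the milligram dose in Table 4.

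**Step 1: does Table 4 agree with itself?**

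- 5 to <8 kg: 1 × 160/20 = 160/20 mg; 1/2 × 320/40 = 160/20 mg; tabulated 160/20 mg.
- 8 to <11 kg: 1.5 × 160/20 = 240/30 mg; 3/4 × 320/40 = 240/30 mg; tabulated 240/30 mg.
- 11 to <17 kg: 1 × 320/40 = 320/40 mg; 17 to <25 kg: 1.5 × 320/40 = 480/60 mg; 25 to <36 kg: 2 × 320/40 = 640/80 mg. All as tabulated.

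The table is consistent in all five bands and in both strengths. It repeats each dose in several ways, so a text-extraction error is an unlikely explanation for the mismatch with the note.

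**Step 2: does the note reproduce the table?**

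| Band | Table 4 (mg) | Note's fraction of 320/40 | Note (mg) | Note ÷ table |
|---|---|---|---|---|
| 5 to <8 kg | 160/20 | 1/4 | 80/10 | 80/160 = 0.50 |
| 8 to <11 kg | 240/30 | 1/2 | 160/20 | 160/240 = 0.67 |

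The ratio is the same for DHA: 10/20 = 0.50 and 20/30 = 0.67. The note fails in both bands.

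**Step 3: compare the gap with within-band weight variation.** Piperaquine per kg at the band limits (the upper weight limit is not itself in the band):

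- 5 to <8 kg: table 160/8 = 20 to 160/5 = 32 mg/kg; note 80/8 = 10 to 80/5 = 16 mg/kg.
- 8 to <11 kg: table 240/11 = 21.8 to 240/8 = 30 mg/kg; note 160/11 = 14.5 to 160/8 = 20 mg/kg.

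The ranges do not overlap in either band. The table exceeds the note by a factor of 2 and 1.5 respectively, while body weight alone produces at most 8/5 = 1.6 and 11/8 = 1.375. The conflict is therefore larger than the natural variation that item 14 assumes.

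These checks show inconsistency only. They do not show which dose is right.

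**The case against.** The note is a conditional fallback. Nothing in the protocol says paediatric tablets were ever unavailable, the section makes the Table 4 schedule the governing rule, and the table already prints full-strength fractions. Staff working from the table or its milligram columns would not need the note. This limits the likelihood of misdosing but does not remove the conflicting instruction.

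A reader might infer that blinded staff could not detect a discrepancy, because an unblinded assistant crushes and packs the doses (section 8.5.3.1). The protocol does not support that. Labels carry the drug dose (section 8.5.3.2), stock is reconciled with usage (section 8.5.3.4), pharmacy staff receive written instructions and training (section 8.5.3.5), and monitors check accountability (section 9.7.1.1). These checks do not guarantee detection, particularly if the written instructions repeat the note, but they rule out a claim that the error would go unseen.

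A reader might also infer that the primary comparison is diluted. The protocol does not give the share of children in these bands, the share given full-strength tablets, or a dose-response relation, so no size can be attached. The intention-to-treat comparison stands as randomised in any case.

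Finally, item 14 is defined by the dose received. A variable built from the amount dispensed would capture a lower dose correctly. Misclassification arises only if mg/kg is computed from Table 4 and body weight.

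**Conclusion.** The contradiction stands and nothing elsewhere in the protocol resolves it. Followed literally, the note gives 50% of the tabulated dose for 5 to <8 kg and 67% for 8 to <11 kg, for both drug components. It is an internal inconsistency, not a design choice.

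The size in milligrams rests only on the tablet contents and fractions printed in the protocol. The consequences rest on two conditions that the protocol does not document: that paediatric tablets were unavailable somewhere, and that the note was used there in place of the table. If both hold, doses could differ within a band by site or supply, and the premise of subgroup item 14 fails. Bias in the primary result is not shown.

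It must be fixed on grounds of safety and clarity: it is a live dosing instruction for the smallest children in a trial that the protocol lists as recruiting.

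The note's milligram doses match those of the two lowest bands in the appended package insert (section 16.8), whose weight limits differ (5 to <7 and 7 to <13 kg), and the version history records an update of Table 4. The note may be left over from an earlier schedule. That is inference, and it does not settle which fraction is right.

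**What to change.** 1. Reconcile Table 4 and its note so that a single full-strength fraction remains for each weight band. The sponsor's clinical team decides which.
2. Notify pharmacy staff at every site, and check that their written preparation instructions carry the reconciled fractions.
3. Check dispensing logs for whether full-strength tablets were used in the two lowest bands and, if so, which fraction was used at each site.
4. Derive the mg/kg variable for subgroup item 14 from the amount actually dispensed and the child's weight, not from Table 4. If the logs show both fractions in use, report that and revise the stated premise that variation is small and due to body weight within bands.

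The cost is a one-line amendment, a notice to pharmacy staff and a log check. Sample size and the primary analysis are unchanged.

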#### 8.5.2.5. Dihydroartemisinin-piperaquine administration

The first dose will be administered crushed and dissolved in water in the clinic or the home of the participant under direct observation. The remaining two doses will be given to take at home during the following two consecutive days. Participant's caretakers will be advised to give the drug to the child at about the same time each day with water. Should a caretaker forget to give the drug dose at the set time, they will be advised to take it as soon as this is realised and to continue the recommended regimen until the dose is completed.

Participants who take DP or placebo in the clinic will be observed for at least 60 minutes. Should a participant vomit within 30 minutes of receiving the treatment drug, the full dose will be re-administered. Should a participant vomit within 30-60 minutes of drug intake, half dose will be re-administered. Repeat dosing will be attempted once and if the second dose is vomited, the participant will receive artemether-lumefantrine. Caretakers will be instructed to inform the study team the same day for a replacement dose if a participant vomits the treatment at home

To minimise QTc prolongation, Sigma Tau, Italy, the manufacturer of this brand of DP (Eurartesim®), advises patients to take the first day's dose approximately three hours after meals as fatty food can increase the absorption of piperaquine. However, overall studies show that DP when given at the

standard dose over 3 days is well tolerated and can be given safely with small amount of food, such as a biscuit.

Recently a review was completed for WHO to evaluate the safety of DP when used for IPT. Across all studies, including 7 trials, monthly DP was associated with a significantly lower risk of SAEs compared to placebo, daily trimethoprim-sulfamethoxazole, or monthly SP. Overall 12 deaths were reported among those exposed to DP and 16 among those exposed to comparator therapies, with no studies reporting any sudden or unexplained deaths.

One trial in children 6m to 24m of age in Uganda, included monthly DP for up to 18 monthly courses. As part of this trial detailed sub-studies of the effect of DP on cardiac repolarization were conducted in 26 children. A total of 183 ECGs were conducted; all of the follow-up ECGs had a QTc < 450msec with a mean QTc = 396msec (range 278-444, SD 31.3). There were no differences in the mean (SD) QTc intervals measured 4-6 hours after the 3rd dose (i.e. peak piperaquine levels) for children who had been prescribed 3-5, 6-10, or 11-18 prior doses of DP: Mean (SD)QTc 405 (26), 388 (33) and 396 (33), respectively. Thus this nested cardiac monitoring study shows that monthly courses of DP is not associated with a trend toward increasing QTc prolongation with increasing number of DP courses. DP also provided superior efficacy compared to placebo or comparators in preventing any parasitaemia in participants (pooled Incidence Rate Ratio 0.22 (95% confidence interval 0.11-0.33)). These limited data on repeat DP exposures suggest that repeat 3-day courses of DP given at monthly intervals over 3 month may be safe and effective and a good option for IPT.

#### 8.5.2.6. Placebo DP

Placebos for DP will be manufactured by Sigma Tau, Italy. The dosage regimen for DP-placebo will be identical in number of tablets per day and timing of the dose to that of the active DP product. The drug administration procedures will also be identical to that for the active drugs.

#### 8.5.2.7. Iron and folate supplementation

All children in both arms, regardless of Hb level, will receive a standardized prophylactic dose of iron supplementation (about 2 mg/kg) from the time of randomisation onwards for a period of about 4 weeks (i.e. until the next dose of PMC-DP is due at 6 weeks). Iron can be given as mono-therapy or as part of the fixed-dose formulation with folic acid.

### 8.5.3. Procedures for Drug handling & Accountability

#### 8.5.3.1. Preparation and packaging

All subject specific study drugs will be crushed and stored in small opaque medicinal containers provided by the sponsor, according to the subject's bodyweight recorded at randomisation. This will be done by a pharmacy assistant who will be unblinded to the study. The full course will be prepared in one session, i.e. 3 containers for a full course of DP or Placebo and will be kept in a subject specific study drug box after preparation until dispensing. Packaging used for all treatment arms will be identical and labelled blinded to the contents.

Just prior to each drug administration, the drugs will be suspended in the opaque container by adding flavoured syrup.

#### 8.5.3.2. Labelling of trial drug

Labelling will be in English and the local language and in accordance with local regulations for each participating country, which will include the name of the study, name and study identification number of the participant, drug dose and may also include usage directions and staff contact number, precautionary measures to be observed when taking the drug.

#### 8.5.3.3. Product Storage

All study drugs will be stored in a secure area with access limited to Investigator and authorised study site personnel, and under appropriate storage conditions. A description of the appropriate investigational product-specific storage conditions are specified on the investigational product pack label.

#### 8.5.3.4. Product accountability

The site-PI will be responsible for establishing a system for the correct handling of study drug to ensure that:

1. Deliveries of study drug from the sponsor are correctly received by a responsible person (e.g. pharmacist assistant)
2. Accurate records are maintained for the receipt of study drug, for the dispensing of study drug to subjects and for returned drug.
3. Certificates of delivery and return must be signed preferably by the investigator or authorised personnel and copies retained in the investigator file.
4. Study drug is to be handled and stored safely and properly and in agreement with the given storage instructions.
5. The study drug is to be prescribed only by the principal investigator, co-investigators or study site personnel authorised to do so by the principal investigator.
6. Study drug is dispensed only to study subjects in accordance with the protocol.
7. Subjects must return all unused medication and empty containers to the investigator.
8. At the end of the study, delivery records must be reconciled with records of usage and returned stock. Any discrepancies must be accounted for in writing.
9. Once accounted for any returned and unused study treatment at the site will be returned to the sponsor for destruction or destroyed locally upon agreement with the sponsor. Drug destruction certificates will be issued that refers to the subject study numbers for subject specific medication that was destroyed.

#### 8.5.3.5. Pharmacist assistant/dispenser

All efforts will be made for the preparation, packaging and labelling of the blinded study drug to be performed and documented in accordance with Good Manufacturing Practice (GMP). The sponsor will provide the pharmacist assistant with written instructions and GMP training on the preparation, packaging and labelling procedures.

### *8.5.4. Removal of Patients from Therapy or Assessment*

Patients can discontinue from the study for any one of the following reasons.

1. Screening error resulting in incorrect enrolment (found that subject did not meet required inclusion / exclusion criteria)

2. Withdrawal of consent at any stage or subject not willing to continue in the study / voluntary discontinuation by the subject
3. Suspected or confirmed allergic reaction to the study drug (removal from therapy only)
4. Safety reasons as judged by the investigator, study safety monitor or Data Monitoring and Ethics Committee (DMEC) (removal from therapy only)
5. [Cardiac monitoring sub-study] At randomization, clinically significant ECG abnormality, defined as QTc interval of >450 ms or evidence of other clinically significant ECG abnormalities, including arrhythmias, ischemia, or evidence of heart failure.
6. [Cardiac monitoring sub-study] After randomization in children who have started receiving PMC; onset of grade 2-4 ECG abnormalities, confirmed after repeat testing.
7. Other

The parents or guardian of subjects who discontinue from the study treatment or from the study entirely will always be asked about the reason(s) for their discontinuation and the presence of adverse events. If a subject discontinues it should be established whether the subject:

1. Discontinues the study treatment, but continues their consent for the data capture up to that point, and to continue follow-up. These subjects will be considered 'off study drug/on study' and where feasible will follow the same schedule of events as those who continue the study intervention, except any adherence assessment. All of these children will be followed until study end at 6 months from enrolment.
2. Discontinues all future activities in the study, but continues their consent for the data captured up to that point to be used in the research
3. Discontinues all future activities in the study and withdraws consent for any data captured to be used for the research

Every effort will be made to follow-up patients who discontinue due to drug related adverse events in order to determine the final outcome. If a subject discontinues due to drug-related adverse events, all the assessments will be conducted that would have been carried out at the next scheduled visit at 6 month (unless consent is withdrawn). This will be recorded in the Case Record Forms (CRFs). The study drug will be returned by the subject. Subjects that have discontinued the study prematurely will not be replaced.

#### *8.5.5. Discontinuation from storage of blood for future studies*

If a subject discontinues it will also be established whether the subject:

1. Continues their consent for long term storage of the blood sample
2. Withdraws consent for long-term storage (for future studies and for genetic testing that is part of the main study protocol, but that may not yet have been conducted for that individual child) before anonymization of the dataset has occurred.

When a subject's consent for long-term storage is withdrawn, the stored sample will be destroyed and the withdrawal noted in the CRF. If the request is received after the dataset has been anonymised, the stored sample can no longer be withdrawn.

### *8.5.6. Adherence to study intervention protocol and strategies for retention*

#### **8.5.6.1. Adherence to study protocol and medication**

At 2, 6 and 10 weeks children will be visited at home or asked to come to the clinic to receive the PMC with DP or placebo. For the home-treatment courses, drug administration of the first daily dose will be given by a study staff or home visitor under direct supervision (day 0). The study staff will instruct the mother to administer the second and third dose around the same time the next two days (days 1 and 2). Care takers of study participants and home visitors will also be reminded through mobile phone contact to take the assigned tablets for the second and third dose. On the last day, some caretakers will be revisited at home by spot checks and asked whether and when the second and third dose was administered. All information will be recorded on the appropriate sections of the CRF.

Subjects judged to be non-compliant may continue in the study but should be counselled on the importance of taking their study medication as prescribed.

#### **8.5.6.2. Strategies for retention**

During screening, parents will be asked whether the child will travel out of the study area for an extended period during the follow-up period. Those who plan 1 month or more away from the study catchment area will be excluded from enrolment. The 'study catchment area' will be defined for each study site before the start of the study. All participants will be reimbursed for transportation costs to and from the clinic.

Detailed directions to the children's homes as well as contact information, including cell phone information, will be recorded prior to discharge. At 18 weeks after enrolment, parents or caretakers will be called or visited at home if no mobile phone contact is possible, to find out about the wellbeing of the study subject as well as remind them to come to the study clinic for the last scheduled visit at week 26. If children do not return for scheduled follow-up visits, the study team will call them and ask them to come to the clinic for evaluation, offering transport reimbursement, or may visit their house to help arrange transport to the clinic if they are willing to come to the clinic, or, alternately, a study staff may go to their home for clinical evaluation and to assess if they still wish to participate in the study.

The caretaker and participant's travel costs will be reimbursed as described in more details in section 11.9, Expenses reimbursement and incentives, page 61.

### *8.5.7. Prior and concomitant therapy*

All concomitant medications taken during the study will be recorded in the appropriate sections of the CRF with indication, dose information, and dates of administration.

#### **8.5.7.1. Permitted Medications during follow up period**

During the treatment and follow-up phase of the study if a subject is diagnosed with malaria the investigator will prescribe antimalarial treatment based on the severity of the malaria illness as indicated in Table 1: Study treatment and phases, page 14.

Use of cotrimoxazole (which has some antimalarial properties) treatment or prophylaxis is not considered prohibited as short-courses are commonly prescribed for the treatment of bacterial infection. Daily cotrimoxazole prophylaxis is used by HIV-infected and exposed children.

#### 8.5.7.2. Concomitant and prohibited Medications

Participants will be counselled to avoid concomitant and prohibited medications, specifically antimalarial drugs not prescribed within the trial protocol, or drugs that may be associated with QTc prolongation.

##### *Prohibited medication*

- Antimalarials not prescribed by the study: Chloroquine, halofantrine, mefloquine
- Diuretics (hydrochlorothiazide, furosemide)
- Drugs known to prolong the QT interval
  - Antimicrobials:
    - macrolides (e.g. erythromycin, clarithromycin, azithromycin, roxithromycin),
    - fluoroquinolones (e.g. ciprofloxacin, norfloxacin, levofloxacin, moxifloxacin, sparfloxacin)
    - pentamidine
  - Antifungals: ketoconazole, fluconazole, itraconazole, posaconazole, voriconazole, caspofungin
  - Antiretrovirals: ARVs, specifically: indinavir, nelfinavir, atazanavir, saquinavir
  - Antiarrhythmic agents (e.g. amiodarone, sotalol)
  - Non-sedating antihistamines (astemizole, terfenadine)
  - Antipsychotics (neuroleptics): Haloperidol, Thioridazine
  - Antidepressants: Imipramine, Citalopram, Escitalopram
  - Antiemetics: Domperidone, Chlorpromazine, Ondansetron

Randomised participants who take prohibited medications resulting in the premature cessation of the study intervention, will remain in the trial and will be included in the primary, intention-to-treat analysis, but excluded from the per-protocol analysis.

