## 8.5. INTERVENTIONS

### *8.5.1. Standard in-hospital and post-discharge care (not study specific or study related)*

All care provided prior to and following enrolment of the patient in the study (at convalescence) will not be part of the study and will be per local (hospital) or national guideline with the exception of the full 3 day course of artemether-lumefantrine (AL) as described below. All details of non-study specific care provided by the hospital staff will be recorded in the study forms, including all drugs and dosages prescribed. The hospital teams providing care will be provided with updates of the latest national and local guidelines for in-hospital care.

*Blood transfusion and malaria treatment:* The standard in-hospital care for severe anaemia includes a blood transfusion (20mL/Kg whole blood or 10 mL/Kg Packed Red cells). In addition, patients suspected to have severe malarial anaemia also receive antimalarial treatment. In patients not able to take oral medication this consists of parenteral artesunate (2.4 mg/Kg at time 0, 12 and 24 hours), followed by a full 3 day course of artemether-lumefantrine (AL) once the patient is able to switch to oral medication. In some instances, when artesunate is not available, patients may receive parenteral quinine (10mg/kg every 8 hours) or i.m artemether. In those children who are able to take oral medication throughout, the 3-day course of AL is given without prior parenteral treatment with artesunate.

*Antibiotics* are commonly used during the in-hospital period and will be documented, but will not be part of the study intervention.

*Iron and folate supplementation* will not be part of the medication provided by the study until the time of randomisation at 2 weeks post-discharge. Until then, the use of haematinic supplementation is at the discretion of the treating clinicians. However, the hospital staff will be reminded that iron supplementation is not required during the first two weeks because the blood transfusion provided as part of the standard in-hospital care will contain adequate amounts of iron for the initial post-discharge period. See section 8.5.2.7, page 31 for details about iron supplementation during the PMC intervention period (i.e. from the first PMC dose at 2 weeks onwards).

*HIV testing*, see section 8.7.3.5, page 38.

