#### *9.2.3.3. Per protocol population*

The per-protocol population is a subset of the ITT population. Subjects with major protocol deviations will be excluded from PP population. Major protocol deviations will be defined in the Statistical Analysis Plan (SAP)

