#### *9.2.5.3. Sensitivity analysis*

A number of sensitivity analyses will be conducted to assess the robustness of the primary endpoint analysis. These include un-stratified Poisson regression models, analysis of the per-protocol subject population, and covariate adjusted analysis. Other regression methods including negative binomial regression and models for recurrent event time data will also be explored. Additional post-hoc analyses may also be conducted if deemed necessary. In addition, the results of the statistical models with and without imputation for missing values for co-variables values will be compared. Covariates for co-variate adjusted analysis and subgroup analysis, and alternative statistical models, which will be specified in the statistical analysis plan (SAP).

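### The per-protocol rule in section 8.5.7.2 drops a whole child on a trigger that can arise at a readmission, so the exclusion can depend on the primary outcome; its size is unknown and its direction conditional

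*Protocol*

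**What the plan says.** The rule stands at the end of the list of prohibited medication in section 8.5.7.2. It applies to "Randomised participants who take prohibited medications resulting in the premature cessation of the study intervention". Such children "will remain in the trial and will be included in the primary, intention-to-treat analysis, but excluded from the per-protocol analysis". Two conditions must be met: a listed medicine was taken, and study drug ended early as a result. The rule does not mention readmission or the setting in which the medicine was given.

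The list includes furosemide, macrolides, fluoroquinolones, azole antifungals and ondansetron. Malaria treatment during follow-up is permitted: under section 8.5.7.1, "the investigator will prescribe antimalarial treatment based on the severity of the malaria illness as indicated in Table 1". Section 8.5.2.1 adds that artemether-lumefantrine given at a readmission shifts the PMC schedule and does not end it. On antibiotics in general, section 8.5.1 says that they "are commonly used during the in-hospital period and will be documented".

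Section 9.2.3.3 gives the general principle: "Subjects with major protocol deviations will be excluded from PP population". It leaves the definition of major deviations to the SAP. Section 9.2.5.3 lists the analyses meant to assess robustness of the primary endpoint analysis: "These include un-stratified Poisson regression models, analysis of the per-protocol subject population, and covariate adjusted analysis".

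The primary outcome (8.6.1) is death or all-cause readmission. The primary analysis (9.2.5.1) is by intention to treat and counts first and repeat events. Item 13 of the subgroup list in 9.2.5.2 hypothesises that PMC works much better in the PMC period (weeks 2 to 14) than afterwards.

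**The concern.** A per-protocol set is informative only if membership does not depend on the outcome being compared. Here it can. A child is readmitted, receives a listed medicine on the ward, study drug is stopped, and the child leaves the analysis with that readmission, every earlier event and all follow-up time. The rule contains no date logic that would keep what happened before the deviation.

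The rule can act only while a course remains to be given. That places the deletions inside the PMC period, where the protocol expects most of the benefit. If more placebo than DP children are readmitted then, more placebo children are removed.

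What is at stake is the reading of a robustness check. If the per-protocol estimate differs from the intention-to-treat estimate, one cannot tell whether the treatment effect is fragile or the exclusion rule produced the gap.

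Although section 9.2.3.3 leaves other deviations to the SAP, this exclusion is already decided in the protocol.

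**Working it through.** The protocol gives no figure for the per-protocol analysis, so there is none to reproduce. Its planning rates (8.8.1.1) do reproduce: 1.152 per child-year × 168/365.25 = 0.530 events per child over 24 weeks, and 0.864 × 168/365.25 = 0.397 (stated as 398 per 1000). The ratio is 0.75.

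**Inputs from the protocol.** Control mean 0.530 events per child over 24 weeks; overall rate ratio 0.75; courses at weeks 2, 6 and 10 after enrolment. With randomisation at week 2, only about the first 8 of the 24 weeks leave a further course to be stopped.

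**Assumptions, because the documents give no figures.**
- A share q of eligible readmissions in those 8 weeks ends study drug through a listed medicine; range 10% to 50%.
- Control events are spread evenly over time, all events are treated as readmissions, and other dropout is ignored.
- Children differ by a gamma frailty with mean 1 and variance θ; θ = 0 or 1.

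**Formula.** Let T be an arm's expected events per child over 24 weeks and L the expected eligible events in the first 8 weeks. A child with frailty Z stays in the set with probability exp(−qLZ). Among those who stay, the mean frailty is 1/(1 + θqL), so

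mean events per retained child = (T − qL) / (1 + θqL).

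The per-protocol rate ratio is the DP value divided by the placebo value.

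**A. Effect confined to the PMC period** (rate ratio 0.50 for 12 weeks, then 1.0), triggers spread over all readmissions. Placebo: T = 0.530, L = 0.530 × 8/24 = 0.1767. DP: T = 0.265 × 0.5 + 0.265 = 0.3975, L = 0.0883. At q = 25% and θ = 1:
- placebo (0.530 − 0.0442)/1.0442 = 0.4653
- DP (0.3975 − 0.0221)/1.0221 = 0.3673
- ratio 0.789, with 4.2% of placebo and 2.2% of DP children excluded.

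**B. Constant rate ratio 0.75**, triggers spread over all readmissions. DP L = 0.1325. With θ = 0 both T and L scale by 0.75, so the ratio is exactly 0.750 for any q, although more placebo children are removed.

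**C. Only non-malaria readmissions trigger** (assumed 40% of control events, unaffected by DP). L = 0.4 × 0.1767 = 0.0707 in both arms. At q = 50%: (0.3975 − 0.0353)/(0.530 − 0.0353) = 0.732. The frailty factor is the same in both arms and cancels.

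| Scenario (true ratio 0.75) | θ | q = 10% | q = 25% | q = 50% |
|---|---|---|---|---|
| A. Effect in PMC period only | 0 | 0.759 | 0.773 | 0.800 |
| A. Effect in PMC period only | 1 | 0.765 | 0.789 | 0.834 |
| B. Constant effect | 0 | 0.750 | 0.750 | 0.750 |
| B. Constant effect | 1 | 0.753 | 0.758 | 0.766 |
| C. Non-malaria triggers only | 0 or 1 | 0.747 | 0.741 | 0.732 |

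**Alternative rule.** Keep the child, count events up to and including the trigger, and censor from there. A simulation of 2 million children per arm gives 0.748 to 0.772 in A, 0.748 to 0.763 in B and 0.749 to 0.751 in C. The simulation error is about 0.001 to 0.002. The same simulation reproduces the table to within about 0.003.

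**The case against.** Three stronger readings are tempting, and the documents do not support them.

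- **That the rule excludes a child because of drugs given at a readmission.** It names a listed medicine in any setting plus cessation of study drug. The list includes outpatient medicines, and the usual antimalarials for a malaria readmission are permitted. The remark on antibiotics in 8.5.1 concerns in-hospital care generally and names no class. Readmission is one route to exclusion, not the rule itself.
- **That the analysis is biased towards no effect.** Unequal removal between arms is not enough, as scenario B shows. Attenuation needs an effect concentrated in the PMC period, frailty, or triggers attached to preventable readmissions. If listed antibiotics go mainly to non-malaria readmissions, the bias reverses.
- **That a 25% reduction could shrink to about 12%.** That figure (rate ratio 0.885) needs q = 50%, complete loss of effect after week 14, frailty variance 1 and triggers over all 12 weeks of the PMC period. The third course is at week 10, so the last 4 weeks leave nothing to stop. A milder waning pattern (0.59, then 0.91) with the 8-week window and frailty variance 1 gives 0.761, 0.778 and 0.811 at q = 10%, 25% and 50%.

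It is also fair to say that excluding children who stopped treatment early is conventional, that the per-protocol analysis is one of several sensitivity analyses, and that section 9.2 lets the SAP supersede the protocol on analysis. These points limit the consequence. They do not remove the defect, because the protocol itself fixes this exclusion and it feeds a named robustness check.

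**Conclusion.** The point holds in a limited form. Section 8.5.7.2 sets a whole-child exclusion on a post-randomisation trigger that can coincide with a primary event, so the per-protocol comparison may be selected on the outcome.

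The size cannot be stated, since it depends on a trigger frequency that the documents do not give. The direction depends on conditions. It is towards no effect under the protocol's own hypothesis of benefit concentrated in the PMC period, if triggers are spread over readmissions (about 0.76 to 0.84 against 0.75). There is little bias under a constant effect (0.75 to 0.77). It is away from no effect if only non-malaria readmissions trigger (0.73 to 0.75). The upper end of the first range needs half of the early readmissions to trigger, for which the protocol offers no support.

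The intention-to-treat primary analysis keeps these children and all their events and is unaffected.

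**What to change.** In 8.5.7.2, and correspondingly in 9.2.3.3 and the SAP, replace whole-child exclusion for this deviation with a dated rule. Keep the child in the per-protocol analysis, count all time and events up to and including any readmission at which the prohibited medicine was given, and censor from the date study drug stopped. Reserve whole-child exclusion for deviations fixed at or before randomisation. This changes the analysis only; the handling of prohibited medicines and of study drug stays as it is.

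The cost is a short text edit. Section 8.5.7 already requires dates of concomitant medicines in the case report form, and section 8.5.4 already keeps children who are off study drug in follow-up to 6 months, so no new data are needed.

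The drawback is that censoring at cessation can still be mildly informative: about 0.75 to 0.77 in the scenarios above, against a true 0.75. The text should therefore say that the per-protocol result is supportive only.
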